# Swedish trial on embolization of middle meningeal artery versus surgical evacuation in chronic subdural hematoma (*SWEMMA*)—a national 12-month multi-center randomized controlled superiority trial with parallel group assignment, open treatment allocation and blinded clinical outcome assessment

**DOI:** 10.1186/s13063-022-06842-4

**Published:** 2022-11-08

**Keywords:** Chronic subdural hematoma, Middle meningeal artery, Embolization, Endovascular, Neurosurgery, Burr hole

## Abstract

**Background:**

Chronic subdural hematoma (cSDH) is one of the most common neurosurgical disorders and the incidence is rising. The routine treatment is neurosurgical hematoma evacuation, which is associated with recurrence rates up to 10–25%. In recent years, endovascular embolization of the middle meningeal artery (eMMA) has garnered much attention due to recurrence rates as low as < 5%. Several randomized controlled trials are planned or ongoing. In most of these trials, conventional neurosurgical treatment with or without adjunctive endovascular embolization is compared. The proposed trial aims to conduct a head-to-head comparison between neurosurgical and endovascular treatment as stand-alone treatments.

**Methods:**

The trial is academically driven and funded within existing public healthcare systems and infrastructure. Patients with uni- or bilateral cSDH, presenting with mild-to moderate symptoms, and admitted to neurosurgery on clinical grounds will be offered participation. Subjects are randomized 1:1 between conventional neurosurgical treatment (control) and endovascular embolization of the middle meningeal artery (intervention). Primary endpoint is reoperation due to clinically and/or radiologically significant recurrence within 3 months. Secondary endpoints include safety, technical success rate, neurological disability, and quality of life.

**Discussion:**

There are mounting retrospective data suggesting eMMA, as sole treatment or as an adjunctive to neurosurgery for cSDH, is safe and effective with a reoperation rate lower than neurosurgical hematoma evacuation alone. If randomized controlled trials confirm these findings, there is a potential for a paradigm shift in the treatment of cSDH where a minimally invasive procedure can replace open surgery in a large and oftentimes old and fragile patient cohort.

**Trial registration:**

ClinicalTrials.gov, ClinicalTrials.gov Identifier NCT05267184. Registered March 4, 2022.

**Supplementary Information:**

The online version contains supplementary material available at 10.1186/s13063-022-06842-4.

## Administrative information

Note: the numbers in curly brackets in this protocol refer to SPIRIT checklist item numbers. The order of the items has been modified to group similar items (see http://www.equator-network.org/reporting-guidelines/spirit-2013-statement-defining-standard-protocol-items-for-clinical-trials/).

## Introduction

### Background and rationale {6a}

Chronic subdural hematoma (cSDH) is one of the most common neurosurgical disorders and the incidence is rising, owing to an aging population and increased use of antithrombotic medications [1, 2]. The mainstay of cSDH treatment is neurosurgical hematoma evacuation, but the method is associated with high recurrence rates and a need for repeat surgery. These rates vary widely in the literature, but with a contemporary international agreement of approximately 10–30% [3, 4].

The hematoma capsule surrounding a cSDH contains highly permeable and fragile capillaries prone to rebleeding [5]. The capsule receives blood supply from the meningeal arteries [6]. In the last 2–3 years an endovascular treatment strategy has garnered much attention, whereby these arteries, and hence the hematoma capsule, are embolized, facilitating humoral hematoma resorption [4].

Several case series and prospective trials using historical controls have shown markedly reduced reoperation rates for endovascular treatment when compared to surgical treatment [7–12]. The reduced reoperation rate has been shown to be consistent for endovascular treatment as stand-alone treatment as well as adjuvant to surgical evacuation (1.7% reoperation rate) compared to surgical treatment alone (27.5% reoperation rate) in matched historical controls [10]. In a study on patients with elevated recurrence risk, a 4% reoperation rate for patients treated with adjuvant endovascular treatment was observed, compared to 14% in a matched historical control group treated by surgical evacuation alone [7]. In a meta-analysis of 888 patients included in 4 trials, the recurrence rate after endovascular treatment (as stand-alone treatment or adjuvant to surgery) was 3.5%, compared to 23.5% for surgical evacuation alone [13]. In a recent retrospective multi-center study, the reoperation rate was 6.5% for stand-alone embolization, compared to 20–30% for conventional surgical treatment [14]. The reoperation rate for endovascular treatment adjunctive to neurosurgical hematoma evacuation may be even lower, but the absolute difference between endovascular treatment as stand-alone treatment or as adjuvant treatment appears small. When used as an adjuvant treatment, the complications of both treatments should also be considered.

Several randomized controlled trials (RCT) are underway, attesting to the rapidly evolving interest in the matter. Most of these trials aim to compare embolization as an adjunct to surgical evacuation or as an alternative to conservative treatment [15]. Thus, current evidence justifies a randomized controlled trial of embolization as a stand-alone alternative to neurosurgical hematoma evacuation in patients with mildly symptomatic cSDH.

### Objectives {7}

Research hypothesis: Embolization of the middle meningeal artery (eMMA) reduces the reoperation frequency of chronic subdural hematoma compared to standard neurosurgical treatment.

#### Study objectives:

Primary objective: To determine if eMMA is superior to standard neurosurgical evacuation in preventing reoperation of cSDH within 3 months.

#### Secondary objectives:

To compare neurological disability (mRS) and quality of life at (EQ-5D) at 3 and 12 months in the two treatment armsTo compare changes in hematoma volume at 3 months after either treatmentTo assess technical success rates of endovascular embolization for cSDHTo compare number and severity of complications between the two treatmentsTo compare long term persistence of effect on reoperation rate and morbidity at 12 months between the two treatment arms

### Trial design {8}

The SWEMMA trial is designed as a randomized, controlled, open, national, multicenter superiority trial with two parallel groups and a primary endpoint of reoperation within 3 months following either procedure. Clinical secondary outcomes assessments at 3 months and 12 months will be blinded. Randomization will be performed in blocks with 1:1 allocation.

## Methods: participants, interventions, and outcomes

### Study setting {9}

The trial is academically driven by local funding. The trial will be conducted at four of Sweden’s University hospitals—Skåne University Hospital in Lund, Sahlgrenska University Hospital in Gothenburg, Karolinska University Hospital in Stockholm, and the University Hospital of Umeå). Combined, these sites provide neurosurgical care for approximately two thirds of the Swedish population and has a yearly average of more than 700 patients operated for cSDH.

### Eligibility criteria {10}

#### Inclusion criteria:

Men and women 18–90 y/oNon-contrast computed tomography (NCCT)- or magnetic resonance imaging (MRI)-verified previously unoperated uni- or bilateral cSDHClinical and/or radiological status indicating neurosurgical treatmentMarkwalder Scale score < 2 [16]Glasgow coma Scale score > 13Able to provide signed informed consent

#### Exclusion criteria:

Acute subdural hematomaFocal, non-hemispheric cSDHMidline shift > 10 mm and/or effaced basal cisterns and/or significant dilatation of one or both lateral ventricle temporal horns and/or incipient uncal herniationStructural pathology causing the cSDH (e.g., dural AV-fistula, AVM, tumor, arachnoid cyst, ventriculoperitoneal shunt)Contraindications to angiographyDependency defined as mRS > 3Life expectancy < 6 monthsComorbidity making follow-up impossibleParticipation in other interventional clinical studyPregnancy

### Who will take informed consent? {26a}

Informed consent will be obtained from every subject by a physician investigator or an authorized designee physician before the clinical research is started. The subject will be informed orally and in writing about all aspects that are relevant to the subject’s decision to participate in the trial, including procedures, risks, and benefits of participation in the clinical research. The informed consent will include an explanation of the trial, duration, explanation of medical record access and patient anonymity, and how coded data may be transferred and used for publications. The informed consent form will contain language that is non-technical and understandable to the patient. Ample time will be provided for the subject to read and understand the informed consent form and to consider participation. The informed consent form will include personally dated signatures of the subject and the principal investigator or an authorized designee physician responsible for conducting the informed consent process. The investigator must inform subjects that they are in a clinical trial, apprise them of their rights as set forth in the informed consent document, and make written documentation that such a discussion took place.

### Additional consent provisions for collection and use of participant data and biological specimens {26b}

This trial does not involve collecting biological specimens for storage. Ancillary studies analyzing clinical and radiological data collected during the trial are outlined in the ethics application approved by the Swedish Ethical Review Authority. Unless waived by the Swedish Ethical Review Authority, any future ancillary studies requiring additional participant consent, will be preceded by a complementary ethical review application.

### Interventions

#### Explanation for the choice of comparators {6b}

Neurosurgical hematoma evacuation is the standard of care for symptomatic cSDH worldwide. Given the inclusion and exclusion criteria of the study, no other potential comparator is applicable.

#### Intervention description {11a}

##### Intervention

Physicians performing the intervention are neuroradiologists with several years of experience in the endovascular field. The procedure is performed under sterile conditions in the angio suite, most commonly under conscious sedation.

Using standard endovascular techniques, arterial access is achieved in the femoral or radial artery. A guiding catheter is advanced to the common (CCA) and external (ECA) carotid arteries of the affected side(s) for baseline angiographic controls and anatomical delineation. A microcatheter is then used for super selective controls of the middle meningeal artery (MMA) for detailed anatomical delineation and then further advanced to a wedged treatment position in an appropriate MMA branch. In preparation, an intra-arterial vasodilating agent, a small dose of local anesthetic, and lastly DMSO are infused in the microcatheter. Under fluoroscopic control, the vessel is embolized with liquid embolysate (Onyx™ or Squid™ or Phil™) until no antegrade flow can be visualized. The process is repeated depending on the number of MMA branches to be treated. Post treatment control angiograms are performed in the ECA and CCA, and arterial access site is closed. An NCCT is performed in the angiolab, and the patient is transferred to neurointensive care unit (NICU) for postoperative controls. Estimated time from vascular access to closure is approximately 1–2 h depending on number of branches and sides to be treated.

##### Control

Neurosurgical hematoma evacuation is a clinical routine treatment performed under sterile conditions in the operating theatre for cSDH. Most commonly, the procedure is performed under local anesthesia and conscious sedation. Depending on patient cooperability, general anesthesia may be indicated. In case of bilateral hematomas in need of simultaneous evacuation, the procedure is performed under general anesthesia. Antibiotic prophylaxis is given preoperatively.

Hair is removed, and a skin incision is made over the parietal or frontal bone (most often), and 1–3 burr holes are made in the skull and conjoined to form a minicraniotomy. The dura is coagulated and incised. The hematoma membrane is punctured when necessary and the hematoma irrigated using a catheter and fluid at room temperature. After evacuation, a small catheter is left in either the subdural space or under the galea, connected to a uribag for either closed, passive (subdural), or active (subgaleal) drainage. The head is slightly elevated, and the cavity is filled with fluid. Subcutaneous sutures secure the galea and subcutis and staples or sutures close the skin incision.

The patient is transferred to the NICU for 4 h of postoperative controls, or possibly overnight, if necessary. Estimated time from skin incision to wound closure is 30 min–1 h. Drainage is left in place for 24 h and then removed. Skin staples are removed after 7–14 days.

In cases of bilateral hematomas, the most expansive side is usually treated first, and the patient is followed clinically and radiologically to ascertain whether contralateral treatment is needed.

#### Criteria for discontinuing or modifying allocated interventions {11b}

Post recruitment violation of inclusion and/or exclusion criteria are grounds for termination from the study. Unfavorable vascular anatomy are grounds for crossing over. Dropouts or crossovers will receive standard treatment as indicated by their clinical status and their data is retained unless explicitly denied.

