#### Strategies to improve adherence to interventions {11c}

The study participants are recommended to follow the study protocol. Given the nature of the trial, deviations from protocol regarding intervention are unlikely to occur. Included participants refusing allocated treatment, and crossovers, will remain in the trial and be included in the intention-to-treat analysis, unless explicitly denied.

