#### Plans to promote participant retention and complete follow-up {18b}

The study participants are recommended to follow the study protocol. Included participants refusing allocated treatment and crossovers will remain in the study and be included in the intention-to-treat analysis. Additional participants may be enrolled to allow the study to meet its designed sample size dimensions to allow for a sufficiently powered per-protocol-analysis.

Participation in this investigation is voluntary, and the subject may withdraw at any time. All enrolled subjects will be included in data analysis unless they withdraw permission for their data to be used. The sponsor will retain and continue to use any data collected prior to the withdrawal of consent, unless specified by the subject.

In the event the subject chooses to withdraw, he/she will be instructed to contact the Investigator immediately. Withdrawal from the investigation will not affect the subject's standard of care. The subject will be informed of any significant information regarding new findings that may develop during the course of the study that may relate to his or her willingness to continue participation as a study subject.

Subjects will participate in their routine follow-up and allow this data to be gathered. If their participation is terminated, any of their data which has been already gathered will continue to be included. The completion of a subject’s participation in the study or early departure from the study must be fully documented in the subject’s medical records. Subjects will be considered discontinued from the study if any of the following occur:Subject voluntarily withdraws from the study: A subject may withdraw consent from study participation at any time. The subject will be offered to give a reason for their withdrawal. If voluntarily given, this reason will be recorded in the eCRF.Subject withdrawn from the study by the investigator: An investigator may withdraw an enrolled subject from the study for the following reason:

If participation in the study is life threatening for the subject or at the investigators own discretion.

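### Terminating patients found ineligible after recruitment can leave randomized patients without the 3-month primary outcome, because nothing says that outcome collection continues

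*Protocol article*

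**What the plan says.** All references are to the protocol article.

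- Criteria for discontinuing or modifying allocated interventions {11b}: "Post recruitment violation of inclusion and/or exclusion criteria are grounds for termination from the study". The rule is not limited to facts that already existed at randomization, and no one blind to arm is named to judge it. The section then treats one angiographic finding differently: "Unfavorable vascular anatomy are grounds for crossing over". For dropouts and crossovers, "their data is retained unless explicitly denied".
- Strategies to improve adherence {11c}: "Included participants refusing allocated treatment, and crossovers, will remain in the trial and be included in the intention-to-treat analysis", subject to the patient not refusing. Section {18b} repeats this. Neither statement names patients terminated for ineligibility.
- Participant retention {18b}: "All enrolled subjects will be included in data analysis unless they withdraw permission for their data to be used". Later in the same section: "If their participation is terminated, any of their data which has been already gathered will continue to be included". An investigator may withdraw a patient if participation is life-threatening "or at the investigators own discretion".
- Outcome collection {18a}: reoperation comes from a national register, checked against medical records, and death from the cause-of-death register, both at 3 months and 1 year.
- Blinding {17a}: allocation is open.

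**The concern.** The primary outcome is reoperation within 3 months. A patient terminated in the first week has, by then, almost none of that outcome gathered. If collection stops at termination, the patient is formally in the analysis but contributes a missing value. The commitment to analyse everyone enrolled then cannot be carried out as written.

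This matters more than ordinary dropout for two reasons. First, the people who decide on termination know the allocation, and one stated ground is discretion alone. Second, one route to late ineligibility is open mainly to one arm. Structural causes such as a dural AV-fistula or AVM are exclusions, inclusion rests on NCCT or MRI, and catheter angiography is described in {11a} as part of embolization but not of surgical evacuation. Missing outcomes could therefore differ between arms for reasons unrelated to chance. Few events are expected in the embolization arm, so a handful of missing outcomes could count.

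**Working it through.** **1. The passages side by side**

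| Patient group | Stays in the study? | In the intention-to-treat analysis? | 3-month outcome still collected? |
|---|---|---|---|
| Refuser or crossover | Yes ({11c}, {18b}) | Yes, stated | Follows from staying in |
| Unfavorable anatomy | Crosses over ({11b}) | Yes, as a crossover | Follows from staying in |
| Ineligible after recruitment | May be terminated ({11b}) | Only through the general rule on all enrolled subjects ({18b}) | Not stated; only data already held are said to be kept |
| Withdrawn at investigator discretion | No ({18b}) | Same general rule | Not stated |

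The gap is in the last column of the last two rows.

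**2. The plan's own sample size**

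Inputs from Sample size {14}: 17% control, 6.5% embolization, two-sided alpha 0.05, power 80%, likelihood ratio test, 144 per arm. With mean rate p̄ = (0.17 + 0.065)/2 = 0.1175 and KL(p,q) = p ln(p/q) + (1−p) ln[(1−p)/(1−q)]:

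n per arm = (z0.975 + z0.80)² / {2[KL(0.17, p̄) + KL(0.065, p̄)]} = 143.06, which rounds up to 144, or 288 in total.

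The stated size reproduces and is not in dispute. A pooled normal approximation puts power at 79.3% with 144 per arm.

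**3. Assumed worst case**

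Expected embolization events: 144 × 0.065 = 9.36. Suppose r patients, all in that arm and all certain to be reoperated, lose their outcome. The observed rate is (9.36 − r)/(144 − r):

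- r = 1: 8.36/143 = 5.8%
- r = 2: 7.36/142 = 5.2%
- r = 3: 6.36/141 = 4.5%
- r = 4: 5.36/140 = 3.8%

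Four patients are 4/144 = 2.8% of the arm but 4/9.36 = 43% of its expected events.

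**4. Less extreme scenarios**

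The documents give no termination rate, so both the fraction f lost (embolization arm only) and the risk among those lost are assumptions. With a true rate of 17% in both arms and risk ρ in the lost patients, the observed embolization rate is (0.17 − fρ)/(1 − f). The false-positive rate of a two-sided 5% test follows from the normal approximation.

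| f (patients) | Power at 17% v 6.5%, loss unrelated to outcome | Spurious difference at ρ = 50% | Type I error at ρ = 50% |
|---|---|---|---|
| 1% (1.4) | 79.1% | 0.3 points | 5.1% |
| 2% (2.9) | 78.9% | 0.7 points | 5.3% |
| 5% (7.2) | 78.1% | 1.7 points | 6.8% |
| 10% (14.4) | 76.8% | 3.7 points | 13.3% |

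Example for 5%: (0.17 − 0.05 × 0.5)/0.95 = 0.1526, a difference of 0.0174 from 0.17. If the lost patients have the same 17% risk as everyone else, type I error stays at 5.0% at every f.

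**The case against.** The strongest reply is that the article already has an all-enrolled rule with a single stated exception, and that {11b} itself retains the data of dropouts. On this view nobody is removed. The sentence on terminated participants says that gathered data stay in; it does not say that collection stops. Because reoperation and death come from registers, no visit is needed to obtain them. All of that stands, and it rules out the claim that the termination rule breaks the intention-to-treat analysis. It does not close the gap, because the article never says that the register look-up happens after termination.

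A reader might also infer that patients who worsen after randomization, and so pass the limits for GCS, Markwalder score or midline shift, would be terminated as ineligible, which would strip out likely failures. The documents do not support this. It treats entry criteria as conditions that must hold throughout; on that reading every evacuated control patient would breach the requirement of no earlier operation. Eligibility is checked before allocation is disclosed ({16b}, {16c}), so the natural meaning is ineligibility discovered later. The wording is loose enough to need tightening, but the worsening route should not carry the argument.

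The angiographic route is narrow as well. The finding that {11b} names, unfavorable anatomy, leads to crossover and not to termination. What remains is a causal fistula or AVM missed at screening, and other criteria could be found violated in either arm.

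Finally, section {20c} plans complete-case analysis, multiple imputation and a per-protocol sensitivity analysis. That these could not repair the loss is not shown. However, the bias check in that section covers only patients who withdraw consent, not those terminated by others.

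**Conclusion.** The point holds as an inconsistency in operative wording that bears on the primary outcome. Sections {11b} and {18b} allow termination for ineligibility or at discretion without securing the 3-month outcome, while {18b} also commits to analysing all enrolled subjects. In an open trial with angiography described for one arm only, the resulting loss could depend on arm.

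Its size is unknown. The fall from 6.5% to between 5.8% and 3.8% assumes that 1 to 4 patients are lost, all from the embolization arm, all certain events and all wholly unobserved; the documents support none of these assumptions. With 1% to 2% lost at an assumed 50% risk, type I error barely moves (5.1% to 5.3%), and it is unaffected if the lost patients have average risk.

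A reader might conclude that the bias most likely favors embolization. The documents do not show this: nothing indicates that patients with an angiographic exclusion would have been reoperated more often than others.

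**What to change.** Reconcile {11b} and {18b} with wording to this effect: ineligibility discovered after randomization, or withdrawal by an investigator, may end study-specific procedures but does not end outcome collection. Every randomized patient stays in the intention-to-treat set in the allocated arm, with reoperation and death taken from the registers at 3 and 12 months. The only exception is a patient who withdraws permission for data use.

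Handle ineligibility in the per-protocol sensitivity analysis already planned in {20c}. Limit it to facts present before randomization, judged by someone who does not know the arm. Report the number terminated, with reasons, by arm.

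The cost is a wording amendment and its approval. The register sources are already planned, and the sample size stays at 288.
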